## Abstract

**Background:**

Delirium occurs frequently in elderly hospitalised patients and is associated with higher mortality, increased length of hospital stay, functional decline, and admission to long-term care. Healthcare professionals frequently do not recognise delirium, indicating that education can play an important role in improving delirium care for hospitalised elderly. Previous studies have indicated that e-learning can provide an effective way of educating healthcare professionals and improving quality of care, though results are inconsistent.

**Methods and design:**

This stepped wedge cluster randomised trial will assess the effects of a complementary delirium e-learning course on the implementation of quality improvement initiative, which aims to enhance the recognition and management of delirium in elderly patients. The trial will be conducted in 18 Dutch hospitals and last 11 months. Measurements will be taken in all participating wards using monthly record reviews, in order to monitor delivered care. These measurements will include the percentage of elderly patients who were screened for the risk of developing delirium, use of the Delirium Observation Screening scale, use of nursing or medical interventions, and the percentage of elderly patients who were diagnosed with delirium. Data regarding the e-learning course will be gathered as well. These data will include user characteristics, information regarding use of the course, delirium knowledge before and after using the course, and the attitude and intentions of nurses concerning delirium care.

**Setting:**

The study will be conducted in internal medicine and surgical wards of eighteen hospitals that are at the beginning stages of implementing the Frail Elderly Project in the Netherlands.

**Discussion:**

Better recognition of elderly patients at risk for delirium and subsequent care is expected from the introduction of an e-learning course for nurses that is complementary to an existing quality improvement project. This trial has the potential to demonstrate that e-learning can be a vital part of the implementation process, especially for quality improvement projects aimed at complex health issues such as delirium. The study will contribute to a growing body of knowledge concerning e-learning and the effects it can have on knowledge as well as delivered care.

**Trial registration:**

Netherlands Trial Register (NTR): NTR2885

## Background

Given the growing number of elderly within most western countries, the increasing attention that has been paid to this subpopulation is not surprising. Combined with the relatively high use of care associated with elderly patients, this development makes the elderly an increasingly important subpopulation for healthcare organisations. Studies regarding patient safety have shown that elderly hospitalised patients are at greater risk for preventable adverse events than younger patients [1,2], indicating that this growing group of patients will bring specific requirements and risks to hospitals.

In the Netherlands, the publication of a report regarding adverse events in Dutch hospitals [2,3] led to the start of a national patient safety programme in 2008 [4]. The programme consists of several themes or projects, one of which is the Frail Elderly Project. This project is an evidence-based improvement project aimed at improving care for hospitalised elderly (aged 70 and over). Four health problems are addressed, namely, delirium, falls, malnutrition, and physical impairment. In the project, participating hospitals are advised to screen all elderly patients directly after admission for frailty, defined as the risk of developing or the presence of these four health problems (Additional file 1) [5-8]. Hospitals are provided with advice regarding the prevention and treatment of these problems as well. The overall aim of the Frail Elderly Project is to reduce preventable functional decline in elderly patients caused by hospital stay by improving the quality of care. The national programme provides participating hospitals with advice concerning the project through conferences, the programme website, and a guide. The programme does not provide implementation support in the participating hospitals themselves; implementation of the projects lies solely with the hospitals. In our study, we focus on the Frail Elderly Project, with specific attention to delirium.

Delirium occurs frequently in hospitalised patients, especially in the elderly: about 25% of hospitalised patients aged 65 and over experience a delirium during their hospital stay [9]. Depending on the population that has been studied and the methods that have been used, the delirium rate can increase to 62% (surgical patients) or even 87% (intensive care) [10]. Delirium, sometimes referred to as acute confusional state, is a temporary neuropsychiatric disorder with physiological causes. A delirious patient will experience disturbance of consciousness and a change in cognition or disturbance of perception [10]. The disorder is noted for its acute onset and fluctuating state [9], which are key features that separate delirium from dementia. However, given the fluctuating state of delirium and the similarities in symptoms with dementia, depression, and psychosis, delirium is sometimes hard to diagnose [9,11], which creates a problem for providing adequate delirium care. Studies have indicated that between 32% and 67% of delirium cases were missed during hospital stay [12]. Under-detection and subsequent inadequate care present a problem because delirium in elderly patients is associated with increased length of hospital stay, functional decline, admission to long-term care, and higher mortality [13,14].

Nevertheless, several studies have shown that a significant percentage of delirium cases are preventable, and different strategies have reduced by approximately one-third the incidence of delirious patients [15-18]. The Frail Elderly Project aims to decrease the incidence of delirium in hospitalised elderly patients and minimise the adverse effects associated with delirium, such as functional decline. As mentioned earlier, the implementation of the Frail Elderly Project is a task of the hospitals themselves; no onsite support or training is provided by the national programme. Because several studies have shown that both physicians and nurses have a lack of knowledge concerning delirium and its recognition [9,19,20], an educational tool would appear to be a valuable supplement to the delirium part of the Frail Elderly Project. That an educational intervention can significantly improve delirium recognition and care has been shown by a previous study, which resulted in a strong decline in delirium point prevalence -- 9.8% in the intervention group versus 19.5% in the control group [21].

Because knowledge about delirium is relevant for virtually all nurses working within the hospital, an educational approach that can improve knowledge and skills for large groups of people is needed. E-learning is one method available for efficiently educating a large number of people. A review by Cook *et al. *[22] has shown that the use of e-learning or 'internet-based education' compared with no intervention is associated with a positive effect on knowledge, skills, and behaviour of healthcare professionals, as well as on patient outcomes. Less clear-cut results have been found for computer-assisted learning aimed at nurses, suggesting more research is needed in this field [23]. Computer-assisted learning refers to all methods of using computerised technology to facilitate education, including e-learning. Whether e-learning can provide a valuable tool for improving delirium care specifically has yet to be determined, though researchers have suggested e-learning as an important option for improving delirium education [24].

The aim of the study is to assess the effects a complementary e-learning course has on the implementation of the delirium part of the Frail Elderly Project, and thus to see whether the use of e-learning improves the provision of delirium care by nurses. The hypothesis underlying this study is that use of e-learning will increase nurses' knowledge regarding delirium and their willingness to change their behaviour regarding at-risk patients. It is hypothesised that these effects will in turn lead to changes in the care provided: screening of elderly patients for risks, observing at-risk patients for delirium, and taking preventative or curative measures. This protocol describes the methodology used in this study and provides details of the stepped wedge cluster randomised controlled trial design [25].

## Methods

### Intervention

For this study, an e-learning course about delirium will be used that is aimed at nursing staff. This course [26] was developed by a commercial publisher (Noordhoff Publishers), in collaboration with a Dutch hospital. The publisher has been approached by the researchers concerning the use of the e-learning course in this study. Prior to selecting the e-learning for this study, the course was reviewed, while still in development, by the researchers and by the Netherlands Centre of Excellence in Nursing. The content of the e-learning course is consistent with Dutch guidelines regarding delirium care [27,28] and the Frail Elderly Project. The Frail Elderly Project has been implemented by Dutch hospitals independently of this study. The selected e-learning course offers hospitals participating in the study the possibility of supporting their implementation with a course that educates nurses in delirium care (one aspect of the project).

The aims of the e-learning course are on the one hand to create or increase awareness about delirium and the associated risks, and on the other hand to increase knowledge about delirium care. The content of the course consists of information regarding delirium, the risks involved for patients, the recognition of at-risk patients and delirious patients, and the prevention or treatment of delirium. By using fictional patient cases, information is provided in a context familiar to nurses. Throughout the course, users are presented with questions concerning previously given information, providing them with insight into the progress they have made.

During the study, the e-learning course will be offered to nurses in the participating wards online for a period of three months. The estimated time needed per nurse to complete the course, including a knowledge test before and after, is four hours. Nurses can stop the course at any time and continue at a later time. When completing the course and the subsequent knowledge test successfully, nurses will be provided with a certificate stating the completed course and the credits awarded. In cooperation with implementation managers of the publisher, 'kick-off' meetings will be organised in each hospital in order to introduce the e-learning course to the users. The aim of these meetings will be to familiarise users with the way the e-learning works and to encourage them to use and complete the course within the three-month period. After one month and again after two months, users who have not completed the course will receive an e-mail reminder concerning the course to further encourage its use [29]. In addition to these personal reminders, each ward will be provided with a monthly overview of use and completion of the e-learning course.

### Setting

Data will be gathered in 18 Dutch hospitals, all of which are at the beginning stages of the implementation of the Frail Elderly Project at the start of the study (self-reported status). These 18 hospitals include two university hospitals, five teaching hospitals, and eleven general hospitals, varying in size (smallest 138 beds, largest 880 beds) and geographical location. One internal medicine ward and one surgical ward of each hospital will participate in the study.

Nearly all hospitals in the Netherlands were initially invited to participate in the study, excluding specialised hospitals such as eye clinics and cancer hospitals, and hospitals already participating in a separate study related to the Frail Elderly Project. The hospitals that responded most quickly to the invitation were included in the study.

### Study design

The study will be conducted using a stepped wedge cluster randomised trial design. The defining feature of this design is that the intervention will be introduced to all clusters -- or in this instance, hospitals -- in a sequential order [25,30,31]. At the start of the study in May 2011, no hospital will have access to the intervention, while at the end in March 2012 all hospitals will have been given access. This offers an advantage over parallel trials, in which certain hospitals would not receive the intervention. The e-learning course is expected to do more good than harm, making it unethical to withhold the intervention from participating hospitals [25,31].

After every monthly data collection moment, one or two new hospitals will receive access to the intervention, as illustrated in Figure 1. The start date at which each hospital is given access to the e-learning course will be randomly assigned, using simple or unrestricted randomisation. Hospitals will each be informed of the start date of the intervention prior to the start of the trial. After a period of 11 months, all 18 hospitals will have received the intervention, and the stepped wedge design will have resulted in gathered data from all hospitals for both the control and the intervention group. This offers an important methodological advantage: each hospital acts as its own control, thereby reducing contamination bias [31].

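### An unrestricted random order of 18 mixed hospitals may by chance cluster hospital types early or late; spreading types over the start dates is a small gain at almost no cost

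*Protocol article*

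**What the plan says.** The Study design section fixes a roll-out by month: "After every monthly data collection moment, one or two new hospitals will receive access to the intervention". At the start "no hospital will have access to the intervention, while at the end in March 2012 all hospitals will have been given access". The start date of each hospital "will be randomly assigned, using simple or unrestricted randomisation", and hospitals are told their date before the trial begins. No restriction by hospital type or size is described. The same section notes that every hospital supplies both control and intervention data and so serves as its own control.

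The Setting section describes the clusters: "These 18 hospitals include two university hospitals, five teaching hospitals, and eleven general hospitals", ranging in size from "smallest 138 beds, largest 880 beds". The Outcomes and data analysis section lists patient-level covariates only. It adjusts for temporal trends and for clustering within hospitals by generalised estimating equations (GEE). Separately, it will analyse hospital type and size among factors that might affect adherence or lead to differences in delivered care.

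**The concern.** In a stepped wedge trial the order of the clusters decides which hospitals supply control data late and intervention data early. With only 18 clusters of three kinds, an order without restriction can put most university and teaching hospitals at one end of the sequence. The protocol itself treats type and size as possible sources of difference in care. Its Discussion adds that the level of implementation reached before the start was not measured and may vary.

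If larger or teaching hospitals take up the background programme at a different pace, a clustered order turns part of that difference in pace into an apparent effect of the course. Hospital type is known before randomisation, so this chance error can be reduced in advance.

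**Working it through.** **Grid.** 18 hospitals x 20 records x 11 months = 3,960 records, which matches the article's total. Eleven monthly measurements, with no hospital exposed at the first and all exposed at the last, give ten crossover points. One or two hospitals at each fits 18: 8 x 2 + 2 x 1 = 18.

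**Two readings of the randomisation phrase.**
- Each hospital draws a date independently: the chance of one or two at every date is C(10,2) x (18!/2^8)/10^18 = 0.0011, or 0.11%.
- The hospitals are put in random order and fill fixed slots: the one-or-two rule is met with probability 1.

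The second reading agrees with the rest of the section.

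**Chance of clustering under a random order** (first nine against last nine hospitals).
- Both university hospitals in the same half: 2 x (9/18) x (8/17) = 0.471.
- Seven non-general hospitals (2 + 5) split 5-2 or worse: 2 x [C(7,5)C(11,4) + C(7,6)C(11,3) + C(7,7)C(11,2)]/C(18,9) = 2 x (6,930 + 1,155 + 55)/48,620 = 0.335.

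**Sampling error.** Assumptions: 20 records per hospital-month, a proportion near 0.5 (midway between the planned 40% and 60%), hospital and month effects in the model, and no further variation between months within a hospital. After those effects are removed, the sum of squares of the intervention indicator is about 15.8 to 16.2, depending on where the single-hospital slots lie. SE = sqrt[(0.25/20)/15.85] = 0.028, or 2.8 points.

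**Error added by the order.** The documents give no figure for a trend difference. Assume that the seven non-general hospitals gain an extra 10 to 30 points linearly over the study. Simulating orders with hospital and month effects in the model gives these SDs of the resulting error:

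| Order | 10 extra points | 30 extra points |
|---|---|---|
| Unrestricted | about 0.4 | about 1.4 |
| Balanced only between early and late halves (4-3) | no improvement | no improvement |
| Spread along the sequence | about 0.2 | about 0.65 |

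The mean error of the unrestricted order is zero.

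**Effect on total error.**
- At 10 points: sqrt(2.8^2 + 0.4^2) = 2.83 unrestricted and sqrt(2.8^2 + 0.2^2) = 2.81 spread, about 1% smaller.
- At 30 points: sqrt(2.8^2 + 1.4^2) = 3.13 and sqrt(2.8^2 + 0.65^2) = 2.87, about 8% smaller.

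**Dependence on the GEE.** Suppose an independence working correlation with month effects (an assumption; the article names GEE only) and a fixed 20-point difference between types. The SD of the order-induced error is then about 4.1 points unrestricted. It is about 0.8 to 0.95 with the seven hospitals spread over the dates, and nearer 2 under a looser, evenly spaced scheme.

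**The case against.** Three stronger readings are tempting, and the documents support none of them.

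- A reader might infer that the method contradicts the schedule. The 0.11% belongs only to independent draws. The section sets out the slots first, with a figure that is not shown here, and then assigns dates, so *unrestricted* most naturally means unstratified. What remains is a wording point.
- A reader might infer that the groups will be unbalanced or the estimate biased. Imbalance is a matter of chance: the university hospitals are split between the halves 53% of the time, and the seven non-general hospitals split 4-3 67% of the time. Unrestricted randomisation is valid and unbiased on average.
- A reader might infer that control and intervention months come from different hospitals. Every hospital supplies both, and time is adjusted for.

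The defence can add that the assumed extra trend is half to one and a half times the whole planned 20-point effect, that the saving in total error is small, and that an article often leaves details of list generation to the full protocol. The first two stand and limit the weight of the point. The third does not dispose of it: the absence of restriction is stated, not omitted.

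**Conclusion.** The point holds as a minor design improvement. The stated method is workable and unbiased on average, but with 18 mixed hospitals it accepts an avoidable chance error. Own-control comparison and adjustment for a common trend do not remove trends that differ by type. A GEE with an independence working correlation would not fully remove fixed differences either.

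Under the assumed type-specific trends of 10 to 30 points, spreading types cuts the SD of this error from about 0.4-1.4 to about 0.2-0.65 points. Beside a sampling error of about 2.8 points, that is roughly 1% to 8% off the total. Without a difference in trend, and with hospital effects in the model, there is nothing to gain. The size rests on the assumed trend; the 47% and 33% rest only on the hospital mix and a random order.

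**What to change.** Before start dates are issued, reword the Study design sentence to say that the 18 hospitals are randomised in order into fixed slots of one or two per date. Restrict the order in two ways:

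- University and teaching hospitals are spread across the whole sequence of dates. Balancing early and late halves alone is not enough.
- The two university hospitals are not both early or both late. This needs its own rule: if the seven are only split 4-3 as one pooled group, both university hospitals still share a half with probability (6 + 3)/21 = 43%.

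The permitted orders should give every hospital the same chance of each slot, so that the restriction introduces no average bias of its own.

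In a sensitivity analysis, add hospital type as a covariate and a hospital-type-by-time term. A main effect of type alone does not address differing trends, and it is redundant where the model already has an effect for each hospital.

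If dates have already been issued, correct the wording and add the sensitivity analysis. The cost is a slightly more complex randomisation list and one extra analysis.

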**Figure 1 F1:**
[figure not shown]
**Diagrammatic illustration of the stepped wedge design**. Each cell represents a moment of data gathering. The dark blue cells represent data gathering in hospitals without e-learning (control period). The light blue cells represent data gathering in hospitals with e-learning (intervention period).

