### Outcomes and data analysis

In the Frail Elderly Project hospitals are advised to screen all elderly patients directly after admission for the risk of developing or the presence of delirium, falls, malnutrition, or physical impairment. The e-learning course educates nurses on screening for delirium. The percentage of elderly patients that are indeed screened for the risk of delirium is the primary outcome of this study. Secondary outcome measures include: the percentage of elderly patients with an increased risk of delirium that are observed with the Delirium Observation Screening scale; the percentage of elderly patients with (an increased risk of) delirium that receive care aimed to prevent or treat delirium; and the percentage of elderly patients that are diagnosed with delirium. Covariates that will be used in the analysis are: age, gender, living situation, comorbidity [36], and admission diagnosis of the patients.

The data analysis will firstly consist of a comparison between hospitals that have received the intervention and hospitals that have not yet received the intervention, according to the stepped wedge schedule. This will be done using multilevel linear regression and multilevel logistic regression analyses. In these analyses, we will adjust for temporal trends and for clustering within hospitals using generalised estimating equations.

Different organisational or system factors that might influence adherence to the intervention or might lead to differences between hospitals in delivered care will be analysed. These factors include hospital type (academic, teaching, general), size, location (urban or rural), and type of records used (paper versus electronic).

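### Course access closes after three months, but one constant effect covers all later readings; under plausible clustering it mainly reflects the open-access months and says little about whether a gain lasts

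*Protocol article*

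**What the plan says.** Three parts of the protocol article bear on this.

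- **Intervention.** The exposure has a fixed end: "During the study, the e-learning course will be offered to nurses in the participating wards online for a period of three months". Kick-off meetings are meant "to encourage them to use and complete the course within the three-month period", and reminders go out after one and after two months.
- **Study design and Figure 1.** "After every monthly data collection moment, one or two new hospitals will receive access to the intervention". The figure itself is not shown, but its legend names only a control state and an intervention state: "The light blue cells represent data gathering in hospitals with e-learning (intervention period".
- **Outcomes and data analysis.** The analysis begins with "a comparison between hospitals that have received the intervention and hospitals that have not yet received the intervention". On the model it adds: "In these analyses, we will adjust for temporal trends and for clustering within hospitals using generalised estimating equations".

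No section separates readings taken while the course is open from readings taken after it has closed. No time-since-access term is named, and the working correlation for the estimating equations is not given.

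**The concern.** The planned contrast treats a hospital as being in one constant state from its start date to March 2012. In fact there are two phases. In the first, nurses can take the course and are reminded to. In the second, the course is closed and what remains is whatever the ward retained.

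One constant effect over both phases assumes that the effect is the same in each. It does not test this. If the assumption fails, the result depends on how the estimator weights each month since access, and those weights need not match the share of records collected. A reader who sees that about half of the intervention records come from after closure could take the single estimate as evidence about the whole intervention period. Whether it is depends on those weights.

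**Working it through.** **Schedule.** The article gives 18 hospitals, 11 monthly readings and about 20 records per hospital per month. Its record total reproduces: 18 × 20 × 11 = 3,960. (Its stated power of 0.8 is not affected by this point.) I assume ten crossings between the 11 readings, with one or two hospitals at each. With a steps of two and b steps of one, a + b = 10 and 2a + b = 18, so a = 8 and b = 2. The position of the two single steps is not given; the base case puts them first and last (1,2,2,2,2,2,2,2,2,1).

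**Cell counts.** Hospital-months at months 1 to 10 since access number 18, 17, 15, 13, 11, 9, 7, 5, 3 and 1, which sum to 99.

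- Open access (months 1-3): 18 + 17 + 15 = 50.
- After closure (months 4-10): 99 - 50 = 49.

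The third reading falls at about the closing date and is counted as open. Across four placements of the single steps, 43 of 91 to 56 of 107 intervention cells (47% to 52%) fall after closure.

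**Weights.** The model is linear, with 11 period effects, one intervention effect, and hospital variance ICC × p(1-p). The residual variance per cell is (1-ICC) × p(1-p)/20, with p = 0.5. The estimate is the intervention element of (X'V⁻¹X)⁻¹X'V⁻¹y. Replacing y by an indicator for month k since access gives that month's weight w_k. The weights sum to 1, and the expected estimate is Σ w_k × (true effect in month k). At ICC 0.05 the ten weights are 0.481, 0.352, 0.224, 0.120, 0.039, -0.020, -0.054, -0.066, -0.054 and -0.022.

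The last column takes a 20-point gain (the article's 40% to 60%) that is full in months 1-3 and zero afterwards. Its true mean over intervention cells is 20 × 50/99 = 10.1 points. If it lasted, every row would read 20.0.

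| Within-hospital correlation | Weight, months 1-3 | Weight, months 4-10 | Estimate if lost at closure |
|---|---|---|---|
| 0 (independence) | 0.70 | 0.30 | 14.0 |
| 0.01 | 0.93 | 0.07 | 18.6 |
| 0.02 | 1.00 | 0.00 | 20.0 |
| 0.05 | 1.06 | -0.06 | 21.2 |
| 0.10 | 1.08 | -0.08 | 21.7 |
| 0.20 | 1.10 | -0.10 | 22.0 |

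A linear calendar trend instead of period effects changes these weights by less than 0.01. Over the four step placements and both trend forms, the post-closure weight is 0.30 to 0.37 under independence, 0.05 to 0.14 at ICC 0.01, and -0.12 to -0.01 at ICC 0.05 to 0.20.

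**With a gradual build-up** (one third, two thirds, then the full 20 points over months 1-3):

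| Correlation | Gain then lasts | Gain lost at closure |
|---|---|---|
| 0 | 14.5 | 8.5 |
| 0.01 | 12.4 | 11.0 |
| 0.05 | 11.2 | 12.4 |

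At 0.05 the lost case is 0.481 × 6.67 + 0.352 × 13.33 + 0.224 × 20 = 12.4; lasting adds -0.058 × 20 = -1.2, giving 11.2. The order of the two cases depends on the correlation.

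**Two phases instead of one.** With separate open and post-closure effects at ICC 0.02 to 0.20:

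- The open-phase standard error is 2.5 to 2.7 points, as for the single effect.
- The post-closure standard error is 3.8 to 4.0 points. This effect rests on 13 hospitals in the base case and 12 to 14 across placements.
- An abrupt change at closure is recovered exactly.
- Gradual change is not. At ICC 0.05, a build-up to a lasting 20 points gives a post-closure estimate of 17.5. A build-up followed by linear decay to zero at month 10 gives 13.8 (open) and 14.1 (closed), against true means of 12.9 and 11.8, so the decay does not appear.

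**The case against.** Four arguments against the point carry weight.

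1. **A trained ward is still exposed.** The article's hypothesis is that the course raises knowledge and willingness, which then change care. Closing the course does not undo that. A reader might infer that the later cells are miscoded; the text does not support this, because a hospital past its three months has indeed received the intervention. This argument stands. The remaining point concerns the single constant effect, not the label.
2. **The size depends on a model the article does not fix.** It names multilevel regression together with generalised estimating equations and states no working correlation. A reader might infer that the planned analysis cannot reveal a loss, or that a vanishing gain always gives the same or a higher estimate than a lasting one. Neither holds in general: under independence, and at a correlation of 0.01, a lost gain gives the lower estimate. This stands and makes the conclusion conditional.
3. **No lasting benefit is promised.** The aim is the effect on implementation, and complete loss at closure is only an illustrative extreme. This stands too: the concern is how the single estimate may be read, not a claim already made.
4. **A fuller analysis plan may add time since access.** It may, and the article says only that the analysis starts with this comparison. But the article does state the two-state contrast, and its figure legend matches it, so the clarification belongs there.

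**Conclusion.** The point holds in a conditional form. The article sets three months of access and one received/not-yet-received effect for all later readings, about half of which fall after closure. With time adjustment and exchangeable correlation of 0.02 to 0.20, those readings have a net weight of 0.00 to -0.10. The single estimate then mostly reflects the open-access months and barely distinguishes a lasting gain from one lost at closure: 20.0 to 22.0 points for the lost gain, against 20.0 if it lasted. At a correlation of 0.01 the weight is 0.07 and under independence 0.30, so a loss would partly show.

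This rests on an assumed step pattern, equal cells of 20 records and a linear model. It does not make the single estimate invalid, and it does not show that any gain is in fact lost.

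**What to change.** In Outcomes and data analysis:

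- Keep the single-effect comparison, and describe its estimate as weighted towards the open-access months.
- Add, with the same adjustment for time and clustering, separate effects against control for access open (readings 1-3 after the start date) and access closed (reading 4 onward).
- Support these with a model in time since access, because two constant phases can hide gradual build-up or decay.
- State the working correlation.
- Base any statement about lasting improvement on the post-closure and time-since-access results together.

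The cost is analysis wording and extra model terms; no new data, sites or visits are needed. The open-phase precision is practically unchanged. The downside is a less precise post-closure effect (standard error about 3.8 to 4.0 points against 2.5 to 2.7) that rests on roughly 12 to 14 of the 18 hospitals.
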